### PARASOL intervention

As written in Chapter 5 the PARASOL intervention will consist of face-to-face appointments as well as online modules. The PARASOL intervention will take 12 weeks with 4-5 face to face sessions with the physical therapist as well as with the mental health nurse and weekly new online modules (see Figure 3 and appendix 2).

### Usual care

Subjects of the control health care centers will get care as usual without any restrictions. They can still receive care (e.g. diagnostic procedures or interventions) of the GP or any other health care professional, including a physical therapist or mental health nurse.

## **8.4 Withdrawal of individual subjects**

Subjects can leave the study at any time for any reason if they wish to do so without any consequences. The investigator can decide to withdraw a subject from the study for urgent medical reasons.

### **8.4.1 Specific criteria for withdrawal**

Not applicable

### 8.5 Replacement of individual subjects after withdrawal

Subjects who withdraw will not be replaced.

### 8.6 Follow-up of subjects withdrawn from treatment

Subjects who withdraw from treatment will be asked to complete the follow-up measurements.

### 8.7 Premature termination of the study

When serious adverse events will be recorded that influence the health of the subjects, we will terminate the study prematurely (see Chapter 9).

[figure not shown]

**Figure 3 Overview of the PARASOL intervention**

## 9. SAFETY REPORTING

### 9.1 Section 10 WMO event

In accordance to section 10, subsection 4, of the WMO, the sponsor will suspend the study if there is sufficient ground that continuation of the study will jeopardise subject health or safety. The sponsor will notify the accredited METC without undue delay of a temporary halt including the reason for such an action. The study will be suspended pending a further positive decision by the accredited METC. The investigator will take care that all subjects are kept informed.

### 9.2 AEs, SAEs and SUSARs

The expectation is that the PARASOL intervention will not lead to (serious) adverse events (AE's or SAE's). However, in case of (serious) adverse events, we will follow the normal procedure as mentioned below.

### **9.2.1 Adverse events (AEs)**

Adverse events are defined as any undesirable experience occurring to a subject during the study, whether or not considered related to PARASOL intervention. All adverse events reported spontaneously by the subject or observed by the investigator or his staff will be recorded.

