**Nature and extent of the burden and risks associated with participation, benefit and group relatedness:** The risks for subjects are expected to be negligible because of the low impact of the PARASOL intervention. The PARASOL intervention has five face-to-face contacts with the physical therapist, four with the mental health nurse and overarching online modules, with content according to the guidelines. Additionally, the burden of the measurements (filling in questionnaires) at baseline and after three and twelve months will take 30-45 minutes. Furthermore, participants have to wear an activity monitor at baseline, after three and twelve months for one week.

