### 5.1 Investigational treatment

#### A. Active face-to-face treatment

The intervention will take 12 weeks with 8-10 treatment sessions, 4-5 sessions per discipline (intake, week 1, 3, 6 and 12). Both the physical therapist and the mental health nurse will have thirty minutes per session. During the intake at both health care professionals, the complaints, treatment demand and negative or maintaining factors of the patient will be identified according to the SCEGS(3). The physical therapist will start with focussing on physical functioning (exercise, stress, pain and fatigue). In the next step the mental health nurse will gradually incorporate psychological and social functioning in the treatment plan. Both health care professionals will integrate cognitive behavioural principles in their part of the intervention. The last session in week 12 will only be with the physical therapist. In this last session, the intervention will be evaluated and long-term goals will be discussed (see Appendix 2 for a schematic view of the PARASOL intervention).

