## **8.3 Study procedures**

### Recruitment of subjects

After randomization of the health care centers, the health care centers will perform the PRESUME screening method using the electronic medical record of the GPs to identify subjects with moderate MUPS. The identified subjects will proactively be approached by the GP by sending them a letter as well as an information letter about the PARASOL study. The GP will send a reminder to the subjects who did not respond two weeks after sending the information letter. Another two weeks later, an assistant of the health care centers will contact the subjects by phone to see if they are willing to participate. When a subject is willing to participate, he can contact the researcher by phone or by mail. The researcher will answer possible questions, give further information, and will ask if the subject is willing to participate. When a subject is willing to participate, an appointment for signing informed consent will be made. After signing informed consent, baseline measurements will be completed (see patient report form) (see Chapter 8.1). After the baseline measurements, subjects of the experimental health care centers will be contacted by phone to make an appointment for the intake with the physical therapist and mental health nurse. Subjects of the control health care centers will be contacted three, six, nine and twelve months after completing baseline measurements for the follow-up measurements. In the meantime, they can receive care as usual (see figure 1). Subjects of the control health care centers will be offered the PARASOL intervention after the last follow-up measurement, twelve months after completing the baseline measurements. When their insurance does not cover the physical therapy part, the PARASOL intervention will be offered for free.

The total duration of the PARASOL study for all subjects (both experimental group and control group) will be twelve months. The PARASOL intervention for the subjects of the experimental group will start after the baseline measurements with an intake at the physical therapist and the mental health nurse and has a duration of twelve weeks.

Besides the above recruitment of subjects we will add two other recruitment strategies to increase the number of subjects. The first strategy is that GPs can recruit patients who are visiting the GP for consultation. The GP can recruit patients according to the following criteria:

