- patients  $\geq 18$  years with  $\geq 5$  general practice consultations during the past twelve months
- GP cannot medically explain the symptoms
- GP already completed the diagnostic phase in accordance with the patient

When a patient is eligible, the GP can give the patient the information letter about the PARASOL study. In addition, the GP will ask if the researchers can contact the patient by phone. If the patient agrees, the GP will inform the researchers and give the name and phone number of the patient.

A second strategy will be an open recruitment in the participating health care centers. Flyers with information of the PARASOL study will be laid down in the waiting rooms. In addition, the flyer will be added in the newsletter of Leidsche Rijn Julius Gezondheidscentra as well as the newsletter of Stichting Gezondheidscentra

Eindhoven and will be send to all patients by mail. Patients who are willing to participate can contact the researcher by phone or by mail. Subsequently, the researcher will contact the GP to check eligibility of the patient according to the above criteria.

Besides the two new recruitment strategies, the GPs in the participating health care centers mentioned that patients had difficulties in understanding the information letter. Therefore, we would like to add the flyer besides sending the letter of the GP and the information letter about the PARASOL study for the remaining 520 patients identified by the PRESUME screening method and selected by the GP.

The researcher will contact the subject by phone to make an appointment for the baseline assessment which will be performed by subjects at home. At the baseline assessment patient report form A will be completed, subjects will be informed and instructed about wearing the Activ8 activity monitor and patient report form B.

Subjects will be asked to carry the Activ8 for one week to measure their physical behaviour as well as requested to complete patient report form B digitally. After one week, they can send the Activ8 back by mail. Subjects are asked to complete the adequate relief question weekly between T0 and T1.

The first follow-up measurement (T1) will be three months after baseline. Subjects will be asked to complete the follow-up measurements and to carry the Activ8 for one week.

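### Adverse events are collected passively while scheduled treatment contact differs by arm (9 sessions against 0 in the first 12 weeks), so raw event counts by arm cannot be compared without bias

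*Protocol*

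**What the plan says.** Section 9.2.1 defines adverse events broadly and for every subject: "Adverse events are defined as any undesirable experience occurring to a subject during the study, whether or not considered related to PARASOL intervention". It then states how they reach the record: "All adverse events reported spontaneously by the subject or observed by the investigator or his staff will be recorded". Table 1 in section 8.3, which summarises all measures, has no adverse event item.

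Scheduled contact differs between the arms.

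- **PARASOL.** The Summary says: "The PARASOL intervention has five face-to-face contacts with the physical therapist, four with the mental health nurse and overarching online modules". Section 5.1 gives the range: "The intervention will take 12 weeks with 8-10 treatment sessions, 4-5 sessions per discipline (intake, week 1, 3, 6 and 12", and adds: "The last session in week 12 will only be with the physical therapist". Appendix 2 agrees with five plus four.
- **Control.** Under Usual care in section 8.3: "Subjects of the control health care centers will get care as usual without any restrictions". No treatment session is scheduled. For follow-up: "Subjects of the control health care centers will be contacted three, six, nine and twelve months after completing baseline measurements for the follow-up measurements".
- **Both arms.** There is a baseline appointment, and then: "Subjects are asked to complete the adequate relief question weekly between T0 and T1". Questionnaires follow at 3, 6, 9 and 12 months (cost questionnaire only at 6 and 9), with a monthly adequate relief question from month 6 to month 12.

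Recorded events have uses. Section 8.7 ties premature termination to serious events that are recorded, and section 9.2.2 sends serious events to the ethics committee in yearly line-listings. Section 9.5 sets up no safety board.

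**The concern.** A passive rule records an event only when someone has occasion to mention it or to see it. Here one arm is given nine such occasions during treatment and the other none, by design. Two arms with the same true event rate would then be expected to show different recorded rates.

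The definition in 9.2.1 covers events in both arms whether or not they are related to the intervention, so a table by arm is a natural product of these data, and readers will compare the columns. An excess under PARASOL could be real or could be an effect of closer observation, and the data could not tell the two apart. A true excess might equally be dismissed as closer observation. The analysis stage cannot repair this, because events that were never asked about cannot be recovered.

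**Working it through.** **1. Count of treatment sessions (section 5.1 and Appendix 2).**

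- Physical therapist: intake and weeks 1, 3, 6, 12 = 5.
- Mental health nurse: intake and weeks 1, 3, 6 = 4.
- Total 5 + 4 = 9. This reproduces the five and four in the Summary and lies within the 8-10 of section 5.1.
- Control arm, same period: 0.

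**2. Scheduled contacts over 12 months (section 8.3).** Add the follow-up contacts at 3, 6, 9 and 12 months, which both arms share:

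- PARASOL 9 + 4 = 13; control 0 + 4 = 4.
- With the baseline appointment: 14 against 5.

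**3. What unequal capture does to the ratio.** Let n be the number per arm, t the true proportion with an event (equal in both arms), and c₁ and c₀ the proportions captured under PARASOL and control.

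- Recorded subjects: n·t·c₁ and n·t·c₀.
- Recorded ratio: (n·t·c₁)/(n·t·c₀) = c₁/c₀.

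The true rate cancels, so only the capture rates matter. The protocol gives no capture rates, so the values below are assumptions. With n = 124 (section 4.4) and an assumed t = 0.30:

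| Capture, PARASOL v control | Recorded subjects | Ratio c₁/c₀ | Fisher p (unclustered) |
|---|---|---|---|
| 60% v 40% | 124 × 0.30 × 0.60 = 22; × 0.40 = 15 | 1.5 | 0.28 |
| 80% v 40% | 124 × 0.30 × 0.80 = 30; × 0.40 = 15 | 2.0 | 0.020 |

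The p-values, unlike the ratio, depend on the assumed t. They also ignore clustering. With the protocol's intraclass correlation of 0.04 and 20 patients per center, the design effect is 1 + (20 − 1) × 0.04 = 1.76. For 30 against 15, the unclustered z of 2.47 becomes 2.47/√1.76 = 1.86, p about 0.06.

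**4. A second illustration, from the contact counts.** Suppose each scheduled contact gives the same chance q of capturing an event, independently. With k contacts, the capture rate is 1 − (1 − q)^k.

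| Assumed q | PARASOL, k = 13 | Control, k = 4 | Ratio |
|---|---|---|---|
| 0.02 | 23% | 8% | 3.0 |
| 0.05 | 49% | 19% | 2.6 |
| 0.10 | 75% | 34% | 2.2 |
| 0.20 | 95% | 59% | 1.6 |

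This model is crude. It treats a treatment session and a questionnaire as equal occasions, ignores when an event happens, and leaves out contacts in usual care. It shows direction, not size.

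**The case against.** The strongest reply is that this is a low-risk behavioural trial which plans no comparison of adverse events. The objectives, the endpoints in 8.1 and the analysis in section 10 contain none. That is correct, so no stated analysis is invalid. The weakness lies in the collection rule and in whatever is later tabulated from it.

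Four further points deserve weight.

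- **Contact in the control arm.** A reader might infer that only PARASOL subjects are scheduled to see study staff. The documents do not support that: both arms have a baseline appointment, a weekly question up to month 3 and follow-up contacts to month 12. The imbalance is in treatment sessions. Control subjects may also see a physical therapist or mental health nurse in usual care, so actual contact with professionals is not zero. The protocol states no route from those professionals to the study record, however.
- **Who counts as staff.** Section 9.2.1 does not say whether the treating therapists are the investigator's staff. If they are, scheduled observation in treatment is 9 against 0. If they are not, what they see has no stated route to the record, though the sessions may still prompt subjects to report. The ambiguity changes the mechanism and the size, and is itself worth settling.
- **The gap in weeks 7 to 11.** Appendix 2 has no session then, and a reader might count this as part of the imbalance. It is not: neither arm has a session in those weeks.
- **Other data on worsening.** Pain, fatigue, 4DKL, EQ5D and RAND-36 are collected alike in both arms at 0, 3 and 12 months, and health care use through the TIC-P at 0, 3, 6, 9 and 12 months. Deterioration is therefore not invisible, but these scores do not replace a record of events.

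**Conclusion.** The concern holds in a limited form. Adverse event collection is passive, no listed study measure asks about events, and scheduled occasions to report or observe them differ by arm: 9 against 0 treatment sessions in the first 12 weeks, and 13 against 4 contacts over 12 months. Raw counts by arm cannot be compared without bias, and the bias most likely runs towards more recorded events under PARASOL.

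The session counts come from the protocol. The size of the bias does not, and is unknown. At equal true rates the spurious ratio equals the ratio of capture rates, 1.5 to 2.0 in the two worked cases. In the milder case the difference is not nominally significant.

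A reader might go further and infer that harms cannot be compared at all, or that the statement of negligible risk is undermined. The documents do not support either. The comparison would be biased rather than impossible, serious events should depend less on visits than minor ones, and the risk statement is an advance judgement of burden, not a hypothesis under test. This is a defect that should be corrected, and it does not touch the primary analysis.

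**What to change.** Amend section 9.2.1 and Table 1 as follows.

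1. Add one identical solicited item in both arms to the existing questionnaires at 3, 6, 9 and 12 months, asking whether there has been a new or worsened health problem or a hospital admission since the last questionnaire and, if so, what.
2. Keep this item apart from the adequate relief form. That form carries a single-question primary outcome, and a question about worsening beside it could affect the answers.
3. Check hospital use reported in the TIC-P against the log of serious adverse events.
4. Base any summary by arm on the solicited item only. List spontaneous and therapist-observed events separately.
5. State whether the treating therapists count as the investigator's staff for 9.2.1.

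**Cost.** A protocol amendment and at most 4 × 248 = 992 extra item responses on forms already sent to everyone, with no new visits. More minor events will be coded and, under section 9.4, followed until they abate or stabilise; in a population defined by its symptoms this is not trivial. Recall over three months is less complete than weekly asking would be. Asking weekly and monthly as well would mean about 20 solicitations per subject, which is hard to justify in a low-risk trial.

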### **9.2.2 Serious adverse events (SAEs)**

The sponsor will report the SAEs through yearly line-listings to the accredited METC that approved the protocol.

### **9.2.3 Suspected unexpected serious adverse reactions (SUSARs)**

Not applicable

## **9.3 Annual safety report**

Not applicable

## **9.4 Follow-up of adverse events**

All AEs will be followed until they have abated, or until a stable situation has been reached. Depending on the event, follow up may require additional tests or medical procedures as indicated, and/or referral to the general physician or a medical specialist. SAEs need to be reported till end of study within the Netherlands, as defined in the protocol.

## **9.5 Data Safety Monitoring Board (DSMB) / Safety Committee**

Not applicable. After consulting the secretary of the internal DSMB, we concluded that due to the low risk of the study an internal DSMB is not indicated.

## **10. STATISTICAL ANALYSIS**

Statistical analysis will be performed with IBM SPSS 22. Statistical analysis will be performed according to the 'intention-to-treat' principle. Any missing values will be imputed with the 'Multivariate Imputation by Chained Equations'.

### **10.1 Primary study parameter**

Differences in effectiveness of the PARASOL intervention will be analysed using longitudinal mixed methods analyses. In this way, we can correct for independence of observations within subjects as well as take into account possible variations between clusters and health care professionals. Analyses will be corrected for potential confounders.

### **10.2 Secondary study parameters**

Statistical analysis of the primary study parameter will also be performed for the secondary study parameters. Furthermore, cost-effectiveness of the PARASOL intervention will be clarified with an incremental cost-effectiveness ratio (ICER) based on

the costs per 'quality adjusted life year (QALY)'. All costs measured by the TIC-P (health care use and indirect costs of illness and absenteeism) are used to calculate the ICER.

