## **3. STUDY DESIGN**

The effectiveness of the blended PARASOL intervention will be studied with a cluster randomized clinical trial with a three and twelve months follow-up period within a primary health care setting. Furthermore, cost-effectiveness will also be assessed six and nine months after baseline using a questionnaire that focus on health care use and indirect costs in the past three months.

[figure not shown]

Figure 1 Overview of the study

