#### 8.1.2 Secondary study parameters/endpoints

Different secondary parameters will be measured to determine the influence of the PARASOL intervention on general health, physical behaviour, perceptions, self-efficacy and cost-effectiveness.

- Severity of symptoms, defined as self-perceived pain and fatigue in the past week, will be measured with an 11-point numeric scale (score 0-10)(50).

- Severity of psychosocial symptoms will be measured with 4DKL questionnaire.

This questionnaire consists of four subscales (distress, depression, anxiety, somatisation)(51,52).

- Health care use and indirect costs through illness and absenteeism will be measured with TIC-P questionnaire to evaluate cost-effectiveness for social perspective in terms of costs per 'Quality Adjusted Life Years (QALYs)(53)'. QALYs will be measured using the SF-6D scores (according to SF-36 questionnaire)(53,54), which is a valid and reliable method(53).

- Physical behaviour will be measured with the Activ8 activity monitor(55). The Activ8 is a valid measurement in detecting lying, sitting, standing, walking, running and cycling. In this way, physical behaviour can be measured accurate. Subjects will wear the Activ8 activity monitor for one week. They can wear the Activ8 activity

monitor in their pants pocket without recharging it during the week. There are accessories as straps available in case subjects does not have pockets.

- Illness perceptions will be measured with the Brief Illness Perception Questionnaire. This questionnaire is an eight-item scale designed to assess cognitive and emotional representations of illness on an ordinal scale (0-10)(56,57).
- Self perceived health will be measured with the EQ5D questionnaire. This questionnaire will measure the perceived health on five levels (i.e. mobility, self-care, usual activities, pain/discomfort and anxiety/depression)(58).
- Self-efficacy will be measured with the Hei-Q questionnaire, which is a user friendly, valid and reliable questionnaire specifically developed in evaluating patients education and self-management programmes in patients with chronic complaints(59).

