Six months and nine months after baseline, subjects will be asked to complete the cost-effectiveness questionnaire, since this questionnaire focuses on health related costs and indirect costs of the past three months. Additionally, subjects are asked to complete the adequate relief question monthly six months after baseline until T2.

The last follow-up measurement (T2) will be twelve months after baseline. Subjects will be asked to complete the follow-up measurements and to carry the Activ8 for one week. Table 1 gives a summary of all measures that will be collected with the different collection points.

Table 1: Summary of measures to be collected

| Primary outcome measures          | Data collection instrument                 | Follow-up measurements                              |       |                                                      |       |        |
|-----------------------------------|--------------------------------------------|-----------------------------------------------------|-------|------------------------------------------------------|-------|--------|
|                                   |                                            | Baseline                                            | 3 mo. | 6 mo.                                                | 9 mo. | 12 mo. |
| Impact of symptoms                | Adequate Relief question                   | X                                                   | X     |                                                      |       | X      |
|                                   |                                            | Weekly between baseline and 3 months after baseline |       | Monthly between six and twelve months after baseline |       |        |
| Quality of life                   | 36-Item Short Form Health Survey (RAND-36) | X                                                   | X     |                                                      |       | X      |
| Secondary outcome measures |                                            |                                                     |       |                                                      |       |        |
| Pain                              | Numeric Rating Scale (NRS)                 | X                                                   | X     |                                                      |       | X      |

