|                                                       |                                                                                     |   |   |   |   |   |
|-------------------------------------------------------|-------------------------------------------------------------------------------------|---|---|---|---|---|
| Fatigue                                               | Numeric Rating Scale (NRS)                                                          | X | X |   |   | X |
| Severity of psychosocial symptoms                     | Four-Dimensional Symptom Questionnaire (4DKL)                                       | X | X |   |   | X |
| General health                                        | EuroQol - 5 Dimensions (EQ5D)                                                       | X | X |   |   | X |
| Physical behaviour                                    | Activ8 activity monitor                                                             | X | X |   |   | X |
| Illness perceptions                                   | Brief Illness Perception Questionnaire (IPQ-K)                                      | X | X |   |   | X |
| Self-efficacy                                         | Health Education Impact Questionnaire (Hei-Q)                                       | X | X |   |   | X |
| Cost-effectiveness                                    | Trimbos and iMTA questionnaire on Costs associated with Psychiatric illness (TIC-P) | X | X | X | X | X |
| Barriers and facilitators of the PARASOL intervention | System Usability Scale (SUS)                                                        |   | X |   |   |   |
| Other measures                                 |                                                                                     |   |   |   |   |   |
| Age                                                   | Questionnaire                                                                       | X |   |   |   |   |
| Gender                                                | Questionnaire                                                                       | X |   |   |   |   |
| Education level                                       | Questionnaire                                                                       | X |   |   |   |   |
| Work situation                                        | Questionnaire                                                                       | X |   |   |   |   |

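### Read literally, the ICER rule in Section 10.2 adds the pre-intervention TIC-P quarter to the follow-up costs, giving 15 months of costs against 12 months of QALYs

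*Protocol*

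**What the plan says.** Section 10.2 defines the effect side of the ICER as costs per QALY and the cost side in one sentence: "All costs measured by the TIC-P (health care use and indirect costs of illness and absenteeism) are used to calculate the ICER". It names no period and no set of questionnaires.

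The other relevant statements are spread over the protocol:

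- **Schedule.** In Table 1 (Section 8.3) the row for the "Trimbos and iMTA questionnaire on Costs associated with Psychiatric illness (TIC-P") has five marks: baseline, 3, 6, 9 and 12 months.
- **Look-back.** Section 3 describes the 6- and 9-month economic assessments as "using a questionnaire that focus on health care use and indirect costs in the past three months". Section 8.3 justifies those two time points "since this questionnaire focuses on health related costs and indirect costs of the past three months". The second statement is about the questionnaire itself, so it applies to the baseline form too.
- **Start of treatment.** Section 8.3: "The PARASOL intervention for the subjects of the experimental group will start after the baseline measurements".
- **Effect side.** Section 8.1.2: "QALYs will be measured using the SF-6D scores (according to SF-36 questionnaire"). Table 1 lists the "36-Item Short Form Health Survey (RAND-36") at baseline, 3 and 12 months.
- **Length of follow-up.** Section 8.3: "The total duration of the PARASOL study for all subjects (both experimental group and control group) will be twelve months".

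**The concern.** The ICER should compare costs and effects over the same period after entry. The four follow-up forms already cover months 0 to 12 without gap or overlap. The baseline form covers the three months before that, when no subject could have received PARASOL. A rule that takes every TIC-P cost brings this quarter into the numerator.

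Any difference between the arms in pre-entry care use or absenteeism would then be added one for one to the incremental cost and reported as a cost or saving of the intervention. In this trial such a difference cannot be taken as negligible:

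- Section 4.4 foresees at least 12 centres, so few units are randomised.
- Sections 8.2 and 8.3 have subjects identified and recruited after their centre's allocation is fixed.
- Section 8.3 adds recruitment by GPs during consultations and by flyer. The criteria for these routes do not repeat the ICPC-code requirement of Section 4.2, so the case mix may differ between centres.

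Even with balanced arms, the extra quarter adds noise to the incremental cost and inflates the mean cost reported for each arm.

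**Working it through.** The protocol states neither a total costing period nor a QALY period, so there is no figure to reproduce. The check builds both from the schedule.

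**1. Periods covered.** A form completed at month t covers (t-3, t).

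| Form | Months covered |
|---|---|
| Baseline | -3 to 0 |
| 3 months | 0 to 3 |
| 6 months | 3 to 6 |
| 9 months | 6 to 9 |
| 12 months | 9 to 12 |

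All five forms: 5 × 3 = 15 months. The four follow-up forms: 4 × 3 = 12 months. The SF-6D source is measured at 0, 3 and 12 months, a span of 12 - 0 = 12 months. The pre-baseline share of the literal sum is 3/15 = 20%.

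**2. Mean cost per arm.** If quarterly costs are level, the literal total is 15/12 = 1.25 times the 12-month total.

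**3. ICER.** Let D0 be the between-arm difference in pre-baseline cost, ΔC the incremental cost over months 0 to 12, and ΔQ the QALY difference. The literal ICER is (ΔC + D0)/ΔQ, so the shift is D0/ΔQ. The protocol gives no value for either term. For assumed values of D0 from -300 to +300 currency units:

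- ΔQ = 0.02: shift up to 300/0.02 = 15,000 per QALY in either direction.
- ΔQ = 0.05: shift up to 300/0.05 = 6,000 per QALY in either direction.
- D0 = 0: no shift.

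**4. Precision.** Assume equal quarterly variance s² and the same correlation r between any two quarters. Then Var(sum of 4) = s²(4 + 12r) and Var(sum of 5) = s²(5 + 20r). If clustering inflates both sums equally (a further assumption), it cancels in the ratio.

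| r | 4 + 12r | 5 + 20r | SE ratio, five to four |
|---|---|---|---|
| 0.3 | 7.6 | 11.0 | √(11.0/7.6) = 1.20 |
| 0.5 | 10.0 | 15.0 | √(15.0/10.0) = 1.22 |
| 0.7 | 12.4 | 19.0 | √(19.0/12.4) = 1.24 |

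**5. Chance imbalance in proportion.** On the same assumptions, the SE of D0 relative to the SE of the four-quarter incremental cost is 1/√(4 + 12r): 0.36, 0.32 and 0.28 for r = 0.3, 0.5 and 0.7. A one-SE chance imbalance before baseline is thus about a third of the standard error that the correct incremental cost already carries.

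**The case against.** The strongest reply is that the word all in Section 10.2 is explained by its own bracket, which lists categories: care use, and indirect costs of illness and absenteeism. On that reading the sentence sets a societal perspective and says nothing about time points. The schedule supports this: Section 8.3 adds the 6- and 9-month forms because of the three-month look-back, which makes sense if the aim was to cover months 0 to 12. A baseline form also has ordinary uses for description and adjustment. This stands as an account of likely intent. The documents therefore do not show that 15 months will in fact be summed. They show only that the rule as worded permits it and that nothing rules it out.

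A second reply is that costing windows belong in an analysis plan, which is not shown here. That would answer a complaint that the protocol is silent. It does not answer this one, because the protocol states an inclusion rule and the rule gives the wrong numerator when followed. The 12-month QALY period is, admittedly, inferred from the schedule and not stated.

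Stronger conclusions that a reader might draw are not supported:

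- **That the ICER is inflated by 25%.** That figure applies to each arm's mean. The added amount cancels in the incremental cost when the arms are balanced before baseline.
- **That the ICER is biased in a known direction.** Under ideal randomisation D0 is zero in expectation. Few centres and recruitment after allocation make an imbalance plausible, but the documents do not show one.
- **That the error costs 34% to 104% in standard error.** Those figures compare the literal sum with a four-quarter model adjusted for baseline cost, √[(5 + 20r)/(4 + 12r - 16r²)]. They combine the error with the gain from an optional adjustment. The error's own share is the 20% to 24% above.
- **That the pre-baseline quarter is unusually expensive.** Section 4.2 selects on consultations over twelve months, and Section 4.3 excludes patients whose diagnostic phase is incomplete. Neither shows a peak in the last three months.

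**Conclusion.** The point holds as a defect in a stated rule. Followed as written, Section 10.2 sets 15 months of costs, three of them before treatment, against QALYs that span 12 months by the RAND-36 schedule. Whether this was intended is open.

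The sure consequence of the literal reading is a mean cost per arm that covers the wrong period. The loss of precision depends on the assumed variances and correlations. The shift in the ICER depends on D0 and ΔQ, for which the protocol gives no values. The issue concerns a secondary economic outcome and does not touch the primary analysis, the sample size or data collection. It is minor, but worth correcting because two fair readings of one sentence give different ICERs.

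**What to change.** Replace the cost sentence in Section 10.2 with wording such as: *Total costs for the ICER are the sum of the TIC-P costs, direct and indirect, reported at 3, 6, 9 and 12 months, and so cover months 0 to 12. Costs reported at baseline, which cover the three months before baseline, are not summed. They enter the model for incremental costs as a covariate.* Stating in the same place that QALYs are calculated over months 0 to 12 would remove the remaining inference.

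The covariate is worthwhile because the data are already collected and it adjusts for pre-entry imbalance instead of adding it to the result. Any analysis plan should carry the same wording, settled before cost data are compared between arms.

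The cost is a small text change and one model term, with no new data, visits or subjects. Reported mean costs will be lower than under the literal reading. If only the four follow-up forms were ever meant to be summed, the totals do not change.
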